## Abstract

**Background:**

Because the clinical patterns and symptoms that persist after a COVID-19 infection are diverse, a diagnosis of post-acute COVID-19 syndrome (PACS) is difficult to implement. The current research project therefore aims to evaluate the feasibility and the practicability of a comprehensive, interdisciplinary, and cross-sectoral treatment program consisting of a low-threshold online screening and holistic assessment for PACS. Furthermore, it aims to evaluate digital interventions and the use of so-called personal guides that may help to facilitate the recovery of PACS.

**Methods:**

This German study consists of a low-threshold online screening for PACS where positively screened participants will be supported throughout by personal pilots. The personal pilots are aimed at empowering patients and helping them to navigate through the study and different treatment options. Patients will then be randomly assigned either to an intervention group (IG) or an active control group (ACG). The IG will receive a comprehensive assessment of physiological and psychological functioning to inform future treatment. The ACG does not receive the assessment but both groups will receive a treatment consisting of an individual digital treatment program (digital intervention platform and an intervention via a chatbot). This digital intervention is based on the needs identified during the assessment for participants in the IG. Compared to that, the ACG will receive a more common digital treatment program aiming to reduce PACS symptoms. Importantly, a third comparison group (CompG) will be recruited that does not receive any treatment. A propensity score matching will take place, ensuring comparability between the participants. Primary endpoints of the study are symptom reduction and return to work. Secondary outcomes comprise, for example, social participation and activities in daily life. Furthermore, the feasibility and applicability of the online screening tool, the holistic assessment, digital trainings, and personal pilots will be evaluated.

**Discussion:**

This is one of the first large-scale studies to improve the diagnosis and the care of patients with PACS by means of empowerment. It is to be evaluated whether the methods utilized can be used for the German and international population.

*Trial registration* ClinicalTrials.gov Identifier: NCT05238415; date of registration: February 14, 2022

**Supplementary Information:**

The online version contains supplementary material available at 10.1186/s12879-022-07584-z.

## Background

By July 15th, 2022, almost 30 million people in Germany have contracted COVID-19 [1]. The diagnosis of COVID-19 is made by detecting the causative SARS Cov-2 virus by PCR testing—the symptoms vary among individuals and affect different organ systems with varying severity and expressions [2, 3]. In addition to COVID pneumonia and lung lesions [4], other organ systems are also affected [5]: For example, neurological symptoms of the so-called neuro-COVID are encephalopathy, infection of the central nervous system, ischemic stroke, and peripheral neurological diseases [6]. Cardiological symptoms can be observed that cause heart failure, myocarditis, cardiomyopathies, cardiac arrhythmias, and heart attacks [7, 8]. Ossification may occur in the musculoskeletal system, especially after long-term ventilation [9]. Psychological consequences can include post-traumatic stress disorder (PTSD), anxiety disorders, and depression [10, 11].

### Diagnosis of the post-acute COVID-19 syndrome

A possible complication or long-term consequence of acute COVID-19 is the occurrence of the post-acute COVID-19 syndrome (PACS, which can be used as synonym for long- and post-COVID) [3]. There are conservative estimates that 4 weeks after the onset of acute COVID-19, about 10% of patients still suffer from symptoms that warrant the diagnosis of post-acute COVID-19 syndrome  [12]. Since there are many different symptoms, this complex diagnosis requires reliable and valid diagnostics for comprehensive symptom clarification, and carefully planned, individual treatment afterwards. Due to the interdisciplinary symptomatology, there is currently no uniform care structure in Germany. Hence, affected patients are mainly treated separately and sequentially by general practitioners and specialists which leads to long waiting times. However, there is no holistic control of a thoroughly necessary intersectoral therapy.

In contrast to the acute infection, there are currently no validated, uniform diagnostic criteria, so that the development and further refinement of scientific evidence for research into this clinical diagnosis is required [13] and the diagnosis of PACS is made as a clinical case definition, that is, in the presence of symptoms like the ones in Fig. 1 depicted.

**Fig. 1 Fig1:**
[figure not shown]
Symptoms of PACS

Such symptoms that occur after COVID-19 and that cannot be explained otherwise, indicate the diagnosis of a PACS to be probable [14, 15]. There are currently different guidelines regarding the timeline of PACS: According to the guidelines by the UK National Institute for Health and Care Excellence (NICE), symptoms that persist for 4 weeks after the detection of the acute disease or new-onset are referred to as long COVID or subacute/ongoing COVID-19 [16]. If the symptoms persist for more than 12 weeks, they are called post or chronic COVID-19 [16]. According to the definition of the World Health Organization (WHO), PACS can be present if symptoms occur “usually 3 months” after the acute infection and last “at least 2 months”. The S1 guideline “Post-COVID/Long-COVID” of the Association of the Scientific Medical Societies in Germany [17] is based on the following criteria for establishing PACS:Symptoms that persist from the acute COVID-19 phase or its treatment,symptoms that have led to a new health limitation, ornew symptoms that have arisen after the end of the acute phase but are understood to be a consequence of COVID-19 disease or worsening of a pre-existing underlying condition.

Among a broad variety of other symptoms, emerging symptoms include fatigue, shortness of breath, cognitive dysfunction, abdominal/chest pain, cough, depression, and altered sense of smell/taste [18]. Many, if not all, of these symptoms, severely affect daily routines in individuals which is why patients desperately seek help from professionals or alternative sources (e.g., [13]). According to a meta-analysis by Augustin et al., PACS is diagnosed when at least one of the following symptoms is present at least 1 to 3 months after the acute infection: inability of smell (anosmia), loss of taste (ageusia), fatigue, or shortness of breath [19]. With these criteria, a PACS diagnosis was made in 27.8% (after 4 months) and 34.8% (after 7 months) of the 958 patients examined [19].

The severity of the course of acute COVID-19 is not a reliable predictor of the occurrence of PACS: An analysis of 28 studies found that 5–36% of outpatients, who had a milder course of COVID-19, and 39–72% of inpatients with a serious trajectory reported post-acute COVID-19 symptoms (PACS) in the first quarter. A high number of symptoms and very explicitly the occurrence of diarrhea or anosmia during the acute infection as well as female sex appear to increase the likelihood for the occurrence of post-acute COVID symptoms [19, 20].

### Consequences for social participation and quality of life

In Bavaria/Germany, where the study is being carried out, about 20,000 patients with PACS are expected according to the data of the Association of Statutory Health Insurance Physicians of Bavaria [21]. Thus, a considerable need for care must be anticipated. In addition to the individual consequences for the affected patients, such as reduced quality of life and poor health, the loss of earnings can have considerable consequences for the individual, their social network, and society in addition to the social security system in Germany (cf. [20]). A survey with 3762 patients found that 7 months after acute COVID-19, only 27.3% were working the same number of hours as before infection, 22.3% were not working at all and 45.6% had reduced their number of hours [18]. Hence, it is crucial that workability and return to work (RTW) are considered in the treatment of PACS. Preventing the loss of employability and restoring workability is a crucial aim in medical rehabilitation which might be an effective treatment option and hence needs to be adapted to the requirements of patients suffering from PACS [22].

Employment and workability are important parts of social participation [23]. Work life poses an imperative indicator of social life which is endangered if societal requirements cannot be fulfilled. Additionally, a reduced cognitive or physical capacity and performance, for example, due to PACS such as fatigue and brain fog can further decrease patients’ social participation, potentially leading to isolation and further deterioration of health and wellbeing. In turn, reduced participation is related to a decrease in mental health and quality of life. Ismael and colleagues have found that approximately 26% of COVID-19 patients suffer from psychological symptoms including stress and PTSD [24] as well as neuro-psychological symptoms such as the inability to concentrate or language impairments [25]. Mental health problems in PACS patients are common and affect patients’ quality of life [26].

A possible management strategy to prevent these detrimental trajectories are health-promoting behaviors including the maintenance of activities of daily living (ADL). It has been hypothesized that self-management in terms of physical activity and healthy diet as part of a behavioral health intervention can positively influence PACS and avoid an exacerbation of symptoms [27]. Hence, it has been added to the WHO self-treatment recommendations [28], but because the exact physiological mechanisms are not sufficiently understood yet, many self-management strategies (such as physical activity or self-medication) should be implemented with caution since some treatments may actually be contraindicative for some patients [29]. Accordingly, patients need to be empowered to consult with their general practitioner and other specialists to get appropriate recommendations and adhere to these recommendations appropriately.

This will be addressed with a proposed framework of a successful recovery process (see Fig. 2) which builds on the Compensatory Carry Over Action Model (CCAM, [30]). The main idea of the CCAM is that experiences and health outcomes like (physical) activity and (social) participation result from different behaviors such as patient behavior and lifestyle behaviors (e.g., smoking-cessation, nutrition, alcohol abstinence and physical activity abbreviated as SNAP—see Fig. 2).

**Fig. 2 Fig2:**
[figure not shown]
Framework of a successful recovery process building on the Compensatory Carry Over Action Model (CCAM, on basis of Lippke et al. [30])

Patient behavior is the kind of actions patients perform to make use of the health care system (searching for and seeing a doctor, asking questions, providing information, adhering to advice and being able to transfer to other life areas such as lessons learnt regarding symptoms, to prevent further health constraints). These action experiences and resulting health outcomes feed back into behavior management by functioning like outcome expectations. Outcome expectancies are for instance, beliefs and attitudes that our own behavior can improve symptoms instead of only expecting the doctor to fix our health issues. Outcome expectancies are important because they have an impact on higher-level goals. Such higher-level goals drive behavior management centrally as individuals can explicitly or implicitly aim for improving their activity, social participation, and well-being by means of performing actions in that sense (Fig. 2).

### Treatment and management requirements

Due to the wide range of symptoms and limited capacities with specialists, the diagnosis is difficult. Accordingly, a low-threshold screening is of PACS needed to determine PACS, i.e., to support the decision-making processes. Once the diagnosis is made, referrals to different specialists must be made to determine treatment. Since the symptoms of PACS vary greatly among patients [15], the therapy must be adapted to the individual and readjusted in iterations over time, which in turn requires management. For the variety of symptoms, several specialists need to be involved whose respective recommendations must be implemented, hence requiring an effective treatment management approach and patient-centered guidance and care.

In addition to outpatient treatment and therapy, the German guidelines recommend (partial) inpatient medical rehabilitation if there are impairments regarding social participation which require multimodal medical and therapeutic treatment [17]. The aim is buffering long-term health impairments, functional limitations, and endangerment of social participation.

Overall, optimal medical care for patients suffering from PACS with the aim of high treatment quality leads to a considerable effort in the coordination of the treatment process. Successful treatment coordination is currently not guaranteed by the existing structures. That is, in the existing structures of the health care system patients usually, first see their primary care practitioner, who will make the appropriate referral if diagnosis and treatment by a specialist are indicated. Due to the diversity of the symptoms, additional specialized post-COVID outpatient clinics have been set up in many hospitals [31] to which patients also can be referred. Such clinics treat patients partly interdisciplinary and partly specialized in the individual disciplines (cf. [31]). Currently there are 81 of such outpatient clinics listed in Germany (from which 11 are in Bavaria). However, this is not sufficient due to the high rate of patients that are affected from PACS. Furthermore, these outpatient clinics are mainly located in urban areas, so care in sub-urban and rural areas is hardly accessible for patients in need, especially if severely limited with their functionality.

In particular, young affected persons, who previously had not been treated due to (actual or perceived) mild course of the disease, from which it is known to possibly still result in PACS [32], are rarely seen at these clinics [18]. This may lead to a delay in medical support. Accordingly, this could harbor the risk of aggravation and possibly chronification of symptoms, resulting in long-term incapacity to work with limited social participation. This in turn can have a negative impact on the continuation or re-entry into society and lead to economic burdens for the individual and the public in general. Thus, actions are needed. The current project will address these concerns in an exemplary area of Bavaria, Germany with the goal to test and to outline the structure, diagnostic and treatment approach nationwide. The *project aim* is to evaluate a comprehensive, interdisciplinary, and cross-sectoral treatment program consisting of a low-threshold online screening and conducting a holistic assessment for post-acute COVID-19 syndrome (PACS). It also aims to prepare a treatment plan for patients that will be augmented by digital interventions and a so-called personal pilot, who will help patients to navigate through their treatment. In case of the feasibility and effectiveness of the methods applied, our approach will be applied to other regions and countries, too.

### The Research Project

The objective of the present study is the early detection of post-acute COVID-19 symptoms (PACS) and subsequently a long-term and sustainable holistic care and support of patients with PACS to avoid long-term illness and chronification, and to enable social participation.

The long-term goals of the study are the dissemination of validated instruments (i.e.g., the online screening) and newly developed treatment approaches (i.e., the digital interventions and a  personal pilot concept) through communication to central stakeholders such as medical associations, health insurance companies, service providers in the outpatient and inpatient sector as well as professional societies and care institutions. In this way, patient care is to be improved beyond the project duration and care services are to be made more efficient.

Hypotheses, which will be tested with this project, are the following:A short *screening* can detect the presence of PACS.A comprehensive* assessment* can validly and reliably determine rehabilitation or remedial needs and the leading rehabilitation indication and be basis of an individual multidisciplinary treatment plan.The more *individualization* the digital therapy offers, the higher the effectiveness in the treatment of PACS.As contact point for all involved parties, a *personal pilot * empowering the patient suffering from PACS can -by means of an interdisciplinary and intersectoral treatment planning- ensure the sustainable management of interdisciplinary treatment.An *interdisciplinary treatment pathway* and the personal pilots empower the patients, so that the patients receive the appropriate diagnosis and treatment, and to actively participate in their own recovery, ensuring patients recover quickly and sustainably from their PACS conditions, increase their functional capacity, reduce incapacity to work and regain participation.

## Methods

### Study design and setting

This longitudinal randomized control trial study will take place in Bavaria in Germany and has three study arms. Specifically, patients will be randomly assigned to an intervention group (IG) or an active control group (ACG, see Fig. 3 for the flow chart). Furthermore, a comparison group (CompG) will be recruited. Whereas the CompG will not receive any treatment, the IG and the ACG will have contacts with a *personal pilot* who will help the patients to navigate the study participation as well as through treatment options and help them seek help for further needs. The personal pilot acts as a contact point for patients and service providers and guides patients through the care process. Furthermore, the personal pilots make sure participants will take part in the study questionnaires by continuously reminding the patients in case they did not fill out the questionnaires.

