**Fig. 3 Fig3:**
[figure not shown]
Flowchart of the study design. *IG* Intervention Group, *ACG* Active Control Group

Patients are invited via primary care physicians, support groups, press releases, and social media. Participants may take part when they show signs of PACS symptoms that last longer than 4 weeks after the acute COVID-19 infection. All participants will first take part in a low-threshold *online screening*. Following the online screening, patients receive direct feedback as to whether they are suitable to take part in the study (i.e., whether there are indicators of risk factors of the presence of PACS). Shortly after the positive screening patients from the IG and ACG receive their first contact with a personal pilot.

Patients from the IG and the ACG will then receive unspecific *digital interventions* (e.g., hygiene recommendations etc.). In the IG, this unspecific digital intervention will be made available to bridge the time to an assessment that takes place in a clinic and in which patients will be assessed by a multiprofessional team of health care professionals. After the assessment, patients in the IG receive digital interventions that aim to meet their individual needs in terms of their physical capacity (i.e., physically very resilient, moderately resilient, barely resilient); patients in the ACG receive digital interventions that are individualized based on the most debilitating symptoms (fatigue, neuro-cognitive symptoms, cardio-respiratory). The digital intervention tools consist of training plans on the one hand and additionally, a chatbot will be developed and made available to complement the interventions on the other hand. This chatbot will answer specific questions of participants, for example, about symptoms or who to contact first, and it will also contain short psychological “learn”, “think”, “do”, exercises to improve participants well-being.

In the IG, a 3-day multidisciplinary *assessment* will be carried out promptly at a clinic to determine the individual need for treatment, the results of which are used as the basis for holistic treatment planning. Possible treatment recommendations are the initiation of rehabilitation, the provision of medical aids, specific therapies, the recommendation of digital health applications, and outpatient treatments.

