Internal diagnostics	• Echography • Carotis-duplex sonography

The results of the assessment for each professional group will be handed to a clinician, who is then able to make a holistic assessment of whether PACS is present or not. These assessments are also summarized to form a holistic treatment plan, which synopsizes the findings and lists the indicated medical and therapeutic measures. These recommendations will be made visible for the personal pilot, and subsequently made available to the attending outpatient doctor.

The prescription of necessary treatments and aids, as well as the recommendation of digital interventions already take place within the framework of discharge management. If the need for a rehabilitation measure is determined, this will be communicated to the patient directly in a way to enable him/her applying for rehabilitation treatment and finding the most appropriate treatment within Germany (also with the help of the personal pilot).

Using such an approach allows us to test Hypothesis 2, that a comprehensive assessment can determine rehabilitation or remedial needs and the leading rehabilitation indication. To assess the applicability of this hypothesis, we will consider a comparison of test–retest reliabilities of the degree of experienced symptoms in the IG compared with the ACG and the CompG. Furthermore, the assessment allows us also to test Hypothesis 5 that an interdisciplinary treatment pathway empowers the patient. To assess the applicability of this hypothesis we will check whether IG, ACG and CompG differ in terms of the development of symptoms, increased activities of daily lives, RTW and increased social participation. To do so, we will consider MANOVA and repeated measurement ANOVA analyses.

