#### 4. Personal pilot

The personal pilots are the first point of contact for all patients who are admitted to the project. Pilots have the qualifications of trained psychologists, social workers/educators, health scientists or health care professionals. They ensure the connection between the project management team providing the outcome from the screening, the specialized clinic conducting the assessment and the patients—both in an anonymized way. A personal pilot is assigned to each patient who was screened positively and who takes part in the study.

The personal pilots contact the patient by phone or email within 4 days after the participant has finished the screening tool. They provide information about the study process. The personal pilot arranges the inpatient assessment in the IG by making the referral to the assessment clinic. In addition, the personal pilot recommends and organizes participation in digital services.

The personal pilot is available throughout the entire process of care, from screening to implementation of the treatment plan. Thus, the pilot supports the patients throughout the entire medical care as a contact point for both the patients and the medical service providers involved. At regular intervals, they contact the study participants in order to reflect on the progress, make qualitative notes of their observations with the patients (e.g., whether there was anything special or unusual to discuss, or what else patients need or want beyond the [digital] interventions that are already provided in the study) and try to motivate the patients also to increase the study commitment of the patients. Their final aim is to empower patients in their coping with PACS and enable them to find and make use of the best treatment. In the final discussion at the end of the study participation, the personal pilot gives recommendations for further care. The personal pilots are trained in motivational interviewing [35, 36].

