As the project aims to evaluate the four components (online screening, personal pilots, assessment, digital interventions, see Fig. 4) and the five hypotheses that were described above, a structured evaluation plan is set up. The study aims to alleviate or resolve PACS, and thus to generally restore physical and mental functioning. In addition, the aim is to resume performance in terms of activity and social participation. Within the framework of a successful recovery process as described in the CCAM (see Fig. 2), the active cooperation of the patient affected is obligatory. That is, the factors motivation, psychological stability/resilience, and coping strategies will also be considered in the evaluation process. Furthermore, the economic situation and personal contextual factors will also be considered. Different indicators are used to conduct the evaluation process. These include participation/drop-out rates at the different measurement points, acceptance, and satisfaction over the course of participation, implementation fidelity, implementation dose, target group achievement as well as a systematic analysis of the mediating processes.

Focus groups or individual interviews with the clinic staff (at least one person per occupational group) and the participating patients are planned with partially standardized guidelines, which are evaluated with the use of a content analysis. In addition, structured, participatory observations are conducted, and the observations are tracked. The process evaluation is intended to provide information on the implementation fidelity (e.g., which contents were implemented and realized as planned?), and implementation dose (e.g., to what extent were all intended contents covered or implemented? Attendance of participants?).

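### Questionnaire reminders are a task of the personal pilots and no reminder route is described for the CompG, so differential non-response may bias the non-randomised comparisons with that group

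*Protocol article*

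**What the plan says.** Under Study design and setting, the protocol article states that "the personal pilots make sure participants will take part in the study questionnaires by continuously reminding the patients" when a questionnaire has not been filled out. The same paragraph says who has a pilot: "Whereas the CompG will not receive any treatment, the IG and the ACG will have contacts with a" personal pilot. The text that follows, on recruitment and patient flow, repeats the division: "Shortly after the positive screening patients from the IG and ACG receive their first contact with a personal pilot". Section 4, Personal pilot, confines the pilots' referral support to the IG and ACG. It also has the pilots contact participants regularly and "try to motivate the patients also to increase the study commitment of the patients".

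Outcomes are self-completed in an online survey tool (Data management and anonymity). All three groups are measured repeatedly, and the CompG enters through its own online links (Evaluation concept). Hypothesis 5 is tested by whether the groups differ: the authors will "check whether IG, ACG and CompG differ in terms of the development of symptoms", and likewise for daily activities, return to work and social participation. Hypothesis 3 uses the same three-group comparison (section 3, Digital therapy offers). The stated safeguard for the CompG is propensity score matching with the IG on person-related criteria, of which age and sex are the examples given. The process indicators include "participation/drop-out rates at the different measurement points, acceptance, and satisfaction over the course of participation".

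**The concern.** The only retention effort that the article describes is delivered by people who are themselves part of the intervention, and it reaches two of the three groups. Both randomised groups have pilots, so only the CompG can show what pilots add, and Hypothesis 5 names the pilots. Unequal follow-up effort thus falls on the contrast that has to carry that claim.

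If CompG members answer later questionnaires less often, and if answering is related to how their symptoms develop, the CompG responders do not represent the CompG. A difference between groups could then appear, or be hidden, without any effect of the programme. Matching balances the groups at entry and does nothing about who is still answering at T4 or T5.

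A second consequence concerns the process indicators. Questionnaire participation at each time point partly reflects how persistently people were reminded, so a difference between groups with and without pilots is not in itself a sign that the programme works or is liked.

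**Working it through.** **Setting the statements side by side.**
- Reminders are sent by pilots (Study design and setting).
- Pilots serve the IG and ACG (Study design and setting; the patient-flow text after it; section 4).
- A reminder route for the CompG is not described.
- CompG outcomes are used in the tests of Hypotheses 3 and 5 (sections 2 and 3).
- The adjustment is matching of IG and CompG at entry (Evaluation concept; Type of statistical analysis used).

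The structural point rests on these statements and on no figure.

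**The plan's own figures.** The article states no expected response or drop-out rate. Its only power figure is 68% for N = 132 (66 IG, 66 ACG), effect 0.15, two-sided alpha 0.05. For a two-group within-between interaction, λ = f²·N·m/(1−ρ). With 0.15 read as f, m = 2 and ρ = 0, λ = 0.0225 × 132 × 2 = 5.94, and power is 67.7%. This agrees with 68% but has no bearing on the present point, because the CompG is not in that calculation.

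**Illustration 1: mean change (all inputs assumed).** Suppose there is no true effect and response follows a probit selection model. Let p be the share responding and r the correlation between propensity to respond and improvement. The bias in a group's mean change, in SD units, is r·φ(z_p)/p.
- φ(z_p)/p is 0.195 at p = 0.90, 0.350 at 0.80, 0.497 at 0.70, 0.644 at 0.60 and 0.798 at 0.50.
- Equal response, 0.90 in both groups: the difference is 0 for any common r.
- IG at 0.90, spurious CompG-minus-IG difference:

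| CompG response | r = 0.1 | r = 0.2 | r = 0.3 | r = 0.5 |
|---|---|---|---|---|
| 0.80 | 0.015 | 0.031 | 0.046 | 0.077 |
| 0.70 | 0.030 | 0.060 | 0.091 | 0.151 |
| 0.60 | 0.045 | 0.090 | 0.135 | 0.224 |
| 0.50 | 0.060 | 0.121 | 0.181 | 0.301 |

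With r positive (improvers keep answering), the error favours the CompG. With r negative (improvers stop answering), every entry changes sign and the error favours the programme.

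**Illustration 2: a binary outcome (all inputs assumed).** Suppose 30% truly recover in every group.
- CompG response 45% among the recovered and 65% among the rest: 0.30 × 0.45 / (0.30 × 0.45 + 0.70 × 0.65) = 0.135/0.590 = 22.9%.
- If IG response is unrelated to outcome, the IG shows 30%, a spurious gap of about 7 points. With 55% against 65% in the CompG: 0.165/0.620 = 26.6%, about 3 points.
- It is more even-handed to let outcome affect response in the IG too. The CompG odds ratio is (0.45/0.55)/(0.65/0.35) = 0.44. Applied in the IG with 88% response among the non-recovered, this gives 76.4% among the recovered. The IG then shows 0.2292/(0.2292 + 0.616) = 27.1%, and the gap falls to about 4 points.
- Reversing who leaves: the CompG shows 0.30 × 0.65 / (0.195 + 0.70 × 0.45) = 0.195/0.510 = 38%, and the IG 0.264/(0.264 + 0.535) = 33%. The spurious gap is about 5 points against the programme.

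The illustrations show that unequal response can matter and that its sign is open.

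**The case against.** **Silence is not proof of absence.** The article is a condensed protocol. It says what pilots do and does not say how CompG members are prompted. They must be reached somehow, since they are measured repeatedly. This stands as far as it goes: one may not assert that the CompG receives no reminders. But the article does more than omit a detail. It assigns reminders to an intervention component that the CompG lacks, and following that procedure gives unequal effort.

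**The pilots might serve everyone.** Section 4 says that "A personal pilot is assigned to each patient who was screened positively and who takes part in the study". Read alone, this could include the CompG. The other statements tie pilots to the IG and ACG, so the sentence should be reconciled with them.

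**A reader might infer that the bias flatters the programme**, because recovered CompG members lose interest. The documents do not support a direction. Patients with fatigue or cognitive symptoms may equally be the ones who stop answering, which would work against the programme. A 7-point spurious benefit also requires that outcome affects response in the CompG only.

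**A reader might infer that drop-out is used as the measure of acceptance.** It is not: the article lists drop-out rates, acceptance and satisfaction as separate indicators.

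**A reader might take the CompG as the untreated natural course.** The article does say "Whereas the CompG will not receive any treatment", but section 3 gives the group voluntary access to the chatbot, so it is not strictly untreated.

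**The CompG comparison is weak anyway**, being non-randomised and separately recruited. That is true, and it limits the weight of this point. It is no reason to add an avoidable source of bias.

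**Conclusion.** The point holds in limited form. The described follow-up effort depends on group, and this may bias the comparisons of IG and ACG with the CompG under Hypotheses 3 and 5. That response will in fact differ is a reasonable expectation, not something the documents establish. Neither size nor direction can be determined from them. Under the assumed response rates above, the error ranges from 0.015 to 0.30 SD in either direction, and it vanishes when response and its relation to outcome are the same in both groups.

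Reminders are the same in the IG and ACG, so this mechanism does not affect the randomised comparison, which is the one the sample size was planned for. The point is worth correcting before data collection because CompG follow-up that is lost cannot be recovered in analysis without untestable assumptions.

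**What to change.** - Send the same automated reminders, on the same days and in the same number, from the online survey tool to IG, ACG and CompG, and say so in the protocol. Pilot reminders may stay as an addition in the IG and ACG; removing them could lower response in the randomised comparison.
- Report questionnaire response by group and time point.
- Add a sensitivity analysis for non-response in the CompG comparisons that allows departures in both directions.
- State that differences in questionnaire drop-out between groups with and without pilots will not be read as an effect of the programme.
- Reconcile the sentence in section 4 on who is assigned a pilot with the statements that tie pilots to the IG and ACG.

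The cost is a contact e-mail address for each CompG member, a small set-up effort and some protocol wording. Some asymmetry will remain, because regular pilot contact is itself meant to raise commitment to the study. That is why the response table and the sensitivity analysis are needed as well as the common reminders.
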